### Adverse Events

It is not expected that participation in this study will lead to an increase in alcohol consumption. Nevertheless, in an adverse event, defined in this study as participants reporting (via the drinks diary or during contact with the research team) that they have consumed more than 25 UK units of alcohol within a 24-hour period, participants will be contacted by the research team, which includes the clinicians ([name], Clinical Psychologist, Head of Research, Combat Stress and [name], Counseling Psychologist, King’s College London), to perform a clinical interview and risk assessment. If concerns remain, a signposting booklet to relevant charities will be provided to the participants. The study clinicians may register an adverse event and withdraw the participants from the study; however, any data collected before withdrawal will be used for analysis.

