### Study Design

This is a two-arm participant-blinded (single-blinded) RCT, which compares a smartphone app (control arm) that includes feedback on baseline self-reported alcohol consumption with a smartphone app (intervention arm) that includes individualized normative feedback, in addition to features designed to enhance participants’ motivation, app interactive feedback, and self-efficacy in modifying their alcohol consumption. We hypothesize that the intervention arm app will be efficacious in reducing alcohol consumption compared with the control arm app. In this study, both the control and intervention arms will be delivered via one smartphone app known as *Drinks*:Ration. Participants in the control arm are given access only to the alcohol consumption feedback on the basis of publicly available health guidance [42] and reminder messaging to consult the feedback. Those in the intervention arm are given full access to the app, which includes all theoretically driven components and messaging (discussed further in the Intervention section). Both arms will be asked to use the app for 28 days. This study is designed such that the control arm structurally resembles the intervention arm but lacks the active ingredients (eg, drinks diary, interactive drinking feedback, and goal setting). This approach was selected to ensure (1) that both groups receive a digital intervention, (2) uniformity and provide relevance to real-world interventions, and (3) that participants are blinded from the study arm they are assigned to. The trial is conducted via the *Drinks*:Ration platform without any need for involvement of the research team, including the collection of informed consent and data collection. The study flow and data collection points are shown in Figure 1.

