The app is compatible with all modern iOS- and Android-supported devices, and no involvement of the research team is required for participant enrolment. Data is collected, managed, and processed using the Google Firebase server infrastructure in London, United Kingdom.

In this study, the intervention arm will receive the app with all functionalities, including push notifications and SMS text messaging. The control arm participants will have access to only the *questionnaire and feedback* module and will not receive any form of personalized messaging, except prompts to complete questionnaires and reminders to review alcohol consumption feedback (see the Message section for more information). Participants in both arms will complete additional questionnaires on their mood and general mental health when responding to the weekly questionnaires. These responses will be used to personalize the content of the app and push notifications and SMS text messaging delivered to the intervention arm only.

Participants in both arms will be asked to use the app for 28 days. After which, they can continue to use the app; however, they will not receive personalized messaging, and the data collected after this point will not be used in the analyses. However, participants will receive a reminder message on day 84 and day 168 to complete questionnaires.

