0	Title: Welcome to *Drinks*:Ration Message: Your signup is complete. Remember to log last week’s alcohol consumption	Intervention
0	Title: Welcome to *Drinks*:Ration Message: Your signup is now complete	Control
2	Title: Time to set a goal? Message: Why not set a goal to reduce the amount you drink? You can start now by clicking on the *goals* tab in the app…	Intervention
7	Title: Drinking Advice Message: Remember to open *Drinks*:Ration for advice on how to make your alcohol consumption	Control
13	Title: Remember the diary Message: Completing the drinks diary each day allows you to see how well you are doing!	Intervention
14	Title: Let us know… Message: Remember to open the app to tell us how you’re doing	Intervention and control
18	Title: Remember to monitor Message: Monitoring what you drink is proven to help you cut down—why not start fresh this week?	Intervention
21	Title: Be aware! Message: It is good to be aware of what you drink. Monitoring your alcohol consumption really can help your health!	Intervention and control
23	Title: Think… Message: Using Drinks:Ration may have changed some of the drinks you usually have. Try and think how you can keep it up!	Intervention
28	Title: Let us know… Message: Please let us know how you’re getting on!	Intervention and control
56	Title: Keep checking in… Message: Please remember to open the Drinks:Ration app	Intervention and control
84	Title: Let us know… Message: Please let us know how you’re getting on!	Intervention and control
112/140	Title: Keep checking in… Message: Please remember to open the Drinks:Ration app	Intervention and control
168	Title: Let us know… Message: Please let us know how you’re getting on!	Intervention and control

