### Follow-Up Procedure and Data Monitoring

The research team will monitor incoming data to ensure that the app is functioning correctly. The research team will not contact participants outside automatic messaging of the app unless they reach out to the research team with queries, for example technical issues, or if they are unsure of how to perform a task with the app.

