A key strength of this study is the collaboration between the charitable sector, academia, and the UK AF, which has enabled the development of *Drinks*:Ration. A further strength includes remote delivery via smartphones, so that there will be no issues with availability or geographical limitations for participants. The app can also be used on iOS and Android devices. However, our app requires an active data connection for the app to function when logging questionnaires to generate normative feedback. This is to operate the personalization algorithms. We anticipate several challenges in this study. First, our ability to recruit and retain sufficient number of participants to power our analysis, as it is known that many of those who have alcohol-related problems are reluctant to seek help to ameliorate their problems. We planned our recruitment approach following the best practice to mitigate this issue. Further, the app has been designed to promote its active use, with frequent reminders, which is expected to promote adherence to the app. Second, we expect that some participants may encounter technical issues related to the app (eg, unable to log drinks and unable to receive notifications) or the mobile device. To mitigate potential technical or mobile device issues, we have undertaken extensive testing across a range of popular mobile devices and we will allow participants to provide in-app feedback that will be regularly monitored by the research team. Third, the impact of COVID-19 on the study, participant recruitment, engagement, or attrition is unknown. The research team will monitor the situation and handle issues as they arise. Finally, we acknowledge that our sample comprises participants who may be undergoing active treatment. To mitigate this risk, we will undertake statistical analyses to compare the control and intervention arms, and, where identified, these differences will be highlighted when reporting the trial.

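### The >25-unit adverse event is detected through a diary that only the intervention arm has, or through almost entirely participant-initiated contact, so event counts and clinical responses are not comparable by arm

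*Protocol article*

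**What the plan says.** The Adverse Events section of the protocol article ties the event to how it comes to light: "participants reporting (via the drinks diary or during contact with the research team) that they have consumed more than 25 UK units of alcohol" within 24 hours. A detected event leads to contact from the team, a clinical interview and a risk assessment. Signposting may follow, and the study clinicians may register the event and withdraw the participant.

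The Study Design section says the control app "lacks the active ingredients (eg, drinks diary, interactive drinking feedback, and goal setting". The Intervention section agrees: "The control arm participants will have access to only the *questionnaire and feedback* module". On use of the app it says: "Participants in both arms will be asked to use the app for 28 days". Table 1 gives a day-13 message, sent to the intervention arm only: "Completing the drinks diary each day allows you to see how well you are doing".

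On contact, the Follow-Up Procedure and Data Monitoring section states: "The research team will not contact participants outside automatic messaging of the app unless they reach out to the research team with queries". Incoming data are watched, but for a technical purpose: "The research team will monitor incoming data to ensure that the app is functioning correctly". The Discussion adds a channel open to both arms: "we will allow participants to provide in-app feedback that will be regularly monitored by the research team". The one team-initiated contact not prompted by an event is an interview of 20 people, 10 per arm. The Study Debrief section places it at the end of follow-up, while Table 2 places the qualitative interviews at day 28.

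Table 2 and the Outcome Measures section have both arms complete the 7-day TLFB, with drinks recorded for each day, at days 0, 28, 84 and 168. The Adverse Events section does not name the TLFB as a source of events.

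**The concern.** A safety event should have the same chance of being found in each arm. Here one of the two detection routes is itself a component of the intervention. Two things are at stake.

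The first is reporting. The article plans to follow the CONSORT checklist, so a listing of events by arm is plausible. Such a listing would mix detection with drinking and could make the app look less safe than it is.

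The second is the clinical response. Participants receive, or have received, support for mental health problems. A very heavy drinking day entered in the diary brings a clinician to the participant. A control has no diary in which to enter such a day. Clinician contact, which may itself change drinking, is therefore also unequal between arms.

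**Working it through.** The article gives no event rate or detection rate, so there is no stated figure to reproduce. The check is to trace each route to the arm that has it.

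| Route | Intervention | Control |
|---|---|---|
| Drinks diary | Yes, with prompts | No |
| Contact started by the participant, including in-app feedback | Yes | Yes |
| Interview (20 people) | Up to 10 | Up to 10 |
| 7-day TLFB, days 0, 28, 84, 168 | Collected, not a trigger | Collected, not a trigger |

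**Direction.** Let the same share p of each arm have a >25-unit day. Let c be the chance that it surfaces through contact, taken as equal in both arms, and d the chance that it surfaces through the diary, independently of contact.

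- Control detected share: p·c.
- Intervention detected share: p·[d + (1 − d)·c].
- Difference: p·d·(1 − c).
- Ratio: 1 + d·(1 − c)/c.

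The ratio exceeds 1 whenever the diary catches anything (d > 0) and contact does not catch everything (c < 1). It grows as c falls, and the no-contact rule keeps c low. Neither c nor d can be obtained from the document, so no numerical ratio is given.

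**Reach of the interview.** It is balanced between arms and covers few people. Ten of the 37 required per arm is 10/37 = 27%. On the recruitment projection, 620 × 0.30 × 0.60 / 2 = 55.8 per arm, and 10/55.8 = 18%. Both are upper limits, because they suppose that every invitee takes part. The stated aim is to learn about use and experience of the app, so disclosure of a heavy day would be incidental. If Table 2 is right, the interview falls before the day-84 primary endpoint; if the Study Debrief section is right, it falls after.

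**What the TLFB could offer.** Three post-baseline administrations of 7 days give 3 × 7 = 21 of 168 days (12.5%). Before day 84, only the day-28 TLFB could lead to a response. It covers 7 of the 28 days of requested app use (25%), whereas the diary can cover all 28. The TLFB is thus a sparse source, but it is the same in both arms.

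**The case against.** The strongest reply is that the >25-unit rule is a clinical-response rule and not an outcome. The article plans no adverse-event comparison, and withholding the diary from controls is deliberate because the diary is an active ingredient. Adding a TLFB trigger would put clinician contact into the control arm before day 84 and could dilute the contrast. Much of this stands. It limits the point to reporting and equal response, and it makes the TLFB trigger a preference. It does not make a by-arm listing interpretable, and it does not give controls a route to the clinical response.

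Nor can the drinks diary be read as including the TLFB: the Messaging section lists questionnaires and the diary as separate sources.

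A reader might infer several stronger things that the document does not support:

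- **That the same TLFB report is handled differently by arm.** It is not, because the TLFB triggers in neither. The asymmetry is the extra channel in one arm.
- **That the primary outcome is materially biased.** Clinician contact could lower drinking in the intervention arm, and withdrawal could remove heavy drinkers from it, but only among detected participants. The plan keeps data collected before withdrawal, analyses by intention to treat, and uses mixed models with multiple imputation where appropriate. Any bias is likely small.
- **That clinician withdrawal ends follow-up.** The article does not say so, and such detail may sit in the full protocol. The request to uninstall the app is described for people who choose to withdraw.
- **That the imbalance has a known size.** Any figure would rest on assumed detection rates.

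**Conclusion.** The point holds as a minor one. Followed as written, the rule gives the intervention arm a detection route that controls lack, and the shared route depends almost wholly on the participant making contact. By-arm counts of registered events, clinical interviews and clinician withdrawals will not be comparable, and at equal true drinking they will fall mainly on the intervention arm. The direction follows from the text, given similar contact behaviour in the two arms and at least some diary use. That the imbalance is more than slight rests on contact rarely revealing such days, which the no-contact rule makes likely but does not quantify. The consequence is for safety reporting and equal clinical response, not for a planned test.

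**What to change.** 1. Base any by-arm count of >25-unit days on the TLFB day entries at days 28, 84 and 168, with day 0 as the pre-exposure baseline, and state that this samples 21 of 168 days. List diary-detected events separately, marked as intervention-only and not comparable between arms. Report clinician contacts and clinician withdrawals by arm. This uses data already collected and costs only wording.

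2. Preferably, also apply the existing >25-unit trigger to TLFB day entries in both arms, leaving the response to the study clinicians. This needs an automated flag on existing data. The downsides are more flags for the clinicians and some clinician contact in controls before day 84, mainly from the day-28 TLFB. Detection would also lag because of the 7-day recall. The gap would narrow but not close, since the diary would still cover days that the TLFB does not.

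If the team declines the second change in order to protect the contrast, it should adopt the first and report the unequal clinical response as a limitation.

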## Introduction

### Alcohol Misuse Burden

Alcohol misuse is common in the UK Armed Forces (AF), with the prevalence higher in the AF than in the general population [1-4]. Research indicates that this trend continues after personnel leave service (*veteran* or *ex-serving* is used interchangeably in the UK) [1,5]. It has been estimated that more than 50% of those who have left the AF meet the criteria for hazardous alcohol use, a score of 8 or above on the Alcohol Use Disorders Identification Test (AUDIT) [3,6].

Research has shown that individuals in the general population underestimate their drinking and do not perceive it as problematic, even at potentially harmful levels [7]. Young males are at particular risk of underestimating their drinking [7]. This pattern is similar among the UK AF, with less than half of UK AF hazardous drinkers recognizing that they have an alcohol problem [8]. There is also a culture of heavy alcohol use in the UK AF, which is encouraged by the social environment and carries on after personnel leave service [4,9,10]. Therefore, leaving service could provide an opportunity to initiate behavior change in settings with less peer pressure to conform to social norms and promote alcohol awareness.

Focusing on personnel who have left service, a similar pattern has emerged for those who are seeking support for mental health problems and consume alcohol to cope. A recent study of treatment-seeking UK service leavers identified that 43% of respondents reported misusing alcohol and that alcohol misuse was commonly comorbid with posttraumatic stress disorder (PTSD) and common mental health difficulties such as anxiety and depression [11]. Alcohol misuse can also have an impact on treatment adherence. Treatment-seeking veterans with alcohol misuse attended fewer mental health appointments and were more likely to have a negative perception of mental health treatment when alcohol misuse is comorbid with depression or PTSD [12]. It is, therefore, important to develop interventions that may target drinking to cope with motivations, which may subsequently enhance engagement with mental health services and improve mental health outcomes.

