#### Baseline Measures

Upon successful registration, participants will complete a baseline questionnaire to assess physical and mental health, health status, resource utilization (eg, visits to hospital because of alcohol, and days in hospital because of alcohol), and sociodemographics (eg, age, gender, ethnicity, employment status, and occupation).

**Table 2 table2:** Summary of measures and data collection timepoints.

Day or measure		0		7		14		21		28		84		168	

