**Questionnaires (Multimedia Appendix 2)**															
	Informed consents		I^a^/C^b^		—^c^		—		—		—		—		—
	Sociodemographic		I/C		—		—		—		—		—		—
	Resource utilization		I/C		—		—		—		I/C		I/C		I/C
	Depression (PHQ2^d^) [53]		I/C		I/C		I/C		I/C		I/C		I/C		I/C
	Anxiety (GAD2^e^) [54]		I/C		I/C		I/C		I/C		I/C		I/C		I/C
	International Trauma Questionnaire for PTSD^f^ [55]		I/C		—		—		—		I/C		I/C		I/C
	Readiness to Change Ruler [56]		I/C		—		—		—		I/C		I/C		I/C
	Self-Efficacy Ruler [56]		I/C		—		—		—		I/C		I/C		I/C
	Alcohol Use Disorder Identification Test [57]		I/C		—		—		—		I/C		I/C		I/C
	World Health Organization Quality of Life-BREF [58]		I/C		—		—		—		I/C		I/C		I/C
	7-day Timeline Follow-Back for alcohol consumption [43]		I/C		—		—		—		I/C		I/C		I/C

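### The only adverse event is one drinking threshold, found by routes that differ between arms, so hospital use and symptom worsening recorded in both arms fall outside adverse event reporting

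*Protocol article*

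**What the plan says.** Methods, Adverse Events, fixes the term for this trial. An adverse event is "defined in this study as participants reporting (via the drinks diary or during contact with the research team", and what must be reported is "that they have consumed more than 25 UK units of alcohol within a 24-hour period". Such a report leads to contact by the team, a clinical interview and a risk assessment. Within that sequence, "The study clinicians may register an adverse event and withdraw the participants from the study". Study Withdrawal and Consent names an adverse event as a reason for withdrawal but adds no second definition.

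Elsewhere the article schedules other health data. Baseline Measures lists "resource utilization (eg, visits to hospital because of alcohol, and days in hospital because of alcohol", and Table 2 repeats resource utilization after baseline, together with PHQ2 (depression), GAD2 (anxiety) and the International Trauma Questionnaire (ITQ, for PTSD), in both arms. On the mood and mental health items answered with the weekly questionnaires, the Intervention section says: "These responses will be used to personalize the content of the app", along with the messages, for the intervention arm only. Follow-Up Procedure and Data Monitoring says incoming data are watched to check that the app works.

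**The concern.** The definition is explicit and closed, so this is not a detail left to a fuller document. Two problems follow.

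First, it is narrow for this population. Participants are or were in treatment for depression, anxiety or PTSD, and the Introduction describes veterans "seeking support for mental health problems and consume alcohol to cope". Alcohol-related hospital use and mental health deterioration are outcomes a reader of the results would expect to see reported as possible harms. Followed as written, the trial could report no adverse events in an arm that had alcohol-related admissions.

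Second, the event that is defined is found by different means in the two arms. A difference in counts, or the lack of one, could reflect how events were detected rather than how often they occurred.

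**Working it through.** This is mainly a comparison of sections. The plan gives no adverse event figure to reproduce.

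**1. Does the definition admit any other event?** Adverse Events lists one criterion and two reporting routes. The clinicians' option to register an event comes after the interview that the threshold report sets off, so it opens no separate route.

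**2. What is collected but falls outside it?** From Table 2:

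| Measure | Arms | Post-baseline days | Points | In the definition? |
|---|---|---|---|---|
| Resource utilization | both | 28, 84, 168 | 3 | no |
| ITQ (PTSD) | both | 28, 84, 168 | 3 | no |
| PHQ2 | both | 7, 14, 21, 28, 84, 168 | 6 | no |
| GAD2 | both | 7, 14, 21, 28, 84, 168 | 6 | no |

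None of the four is a primary or secondary outcome under Outcome Measures.

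**3. Are the two routes equally open in both arms?**
- *Diary.* Study Design names the drinks diary among the ingredients the control app lacks, and Intervention gives control only the questionnaire and feedback module. This route exists in the intervention arm alone.
- *Contact.* Follow-Up Procedure and Data Monitoring rules out contact beyond automatic messages unless the participant gets in touch. The debrief interviews are the planned exception, with 10 invited per arm.
- Control events can therefore surface only through participant-initiated contact or a debrief. Intervention events can also surface from the diary. The 7-day drinking questionnaire, which asks about each day in both arms, is not named as a route.

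**4. Do the sections agree on contact?** Adverse Events says the team will contact a participant who reports the threshold. Follow-Up Procedure and Data Monitoring says the team will not make contact unless approached, and gives no exception for adverse events. For an event found in the diary, the two cannot both be followed.

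**5. Illustrative size.** The article gives no rate of alcohol-related hospital use. Assume 2% to 10% of participants have at least one such visit over 168 days.
- Required sample: 37 × 2 = 74, giving 74 × 0.02 = 1.5 to 74 × 0.10 = 7.4 people.
- Implied by the recruitment figures: 620 × 0.30 = 186 acceptances, and 186 × 0.60 = 111.6 (about 112) after 40% attrition, giving 2.2 to 11.2 people among the 112.

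These are upper bounds on what the adverse event report would miss, because some of these people might also report crossing the threshold.

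**The case against.** Several points on the other side stand.

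- **A reader might infer that these data can never show harm.** The article does not support that. The Statistical and Data Analysis Plan foresees exploratory tests between arms at follow-up without limiting them to named variables, and drinking, AUDIT and WHOQOL-BREF are compared by arm. Worsening could appear there, though not as an adverse event. The stated use of the weekly responses is also not said to be their only use.
- **A reader might infer that the trial's own rationale predicts worse symptoms as drinking falls.** The Introduction says the reverse: it expects that addressing drinking to cope may improve mental health. The case for reporting symptoms rests on who the participants are, not on a predicted harm.
- **It is tempting to say hospital visits should simply be called adverse events.** Under Adverse Events that label sets off team contact, a clinical interview and possible withdrawal, so relabelling would change clinical management and would not be cheap.
- **It is tempting to call the questionnaires an unbiased comparison.** They share a schedule across arms, but they are self-reported and 40% attrition is expected.
- **Oversight.** The Recruitment section gives the charity and the university joint oversight of risks from taking part, with no limit to the drinking threshold. That provides oversight, but it defines no event and no report by arm.
- **Condensation.** A safety table may exist in a fuller plan that is not shown, so its absence here is not the complaint. The complaint is the definition that the article does state.

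**Conclusion.** The point holds as a matter of safety reporting. The stated definition excludes alcohol-related hospital use and deterioration on four instruments that are scheduled in both arms to day 168, at three or six post-baseline points each. The event it does include has a detection route open to one arm only, so its counts by arm cannot support a statement about relative safety. Both conclusions come from the text and need no assumed rate. The figures of about 1 to 7 people among 74, or 2 to 11 among 112, rest wholly on the assumed 2% to 10% and show scale only. The efficacy analysis is not affected. The change should be made, but it is not a reason to hold the trial.

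**What to change.** Leave the existing adverse event definition and its clinical pathway as they are. Add a separate, prespecified harm-reporting category, stated to trigger no clinical action, that reports by arm:

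- the number of participants with any alcohol-related hospital visit or stay reported at days 28, 84 and 168;
- change from baseline in PHQ2, GAD2 and ITQ to day 168, and the number who worsen, with the rule for worsening set before the data are seen;
- the number of respondents behind each figure, by arm and time point, because of the expected attrition.

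State beside any adverse event count that the diary route exists only in the intervention arm, so the counts are not comparable between arms. The study team should also reconcile Adverse Events with Follow-Up Procedure and Data Monitoring on when participants are contacted.

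The cost is protocol wording and one extra safety table. No new data are needed. The downside for the sponsor is that more harms will be reported.
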